### Statistical and qualitative analysis

Quantitative data will be presented descriptively as rates (categorical) and means (continuous). No formal statistical comparisons or hypothesis testing will be conducted. Data will be compared with existing published literature to explore possible signals of patient benefit.

Rapid qualitative analysis will be used to enable important findings emerging from interviews and observations to be identified during the data collection phase in order to inform ongoing optimisations to the feasibility study [13]. Based on initial data collection, a Rapid Analysis Protocol sheet will be developed which will subsequently be used to summarise key data for each interview/observation, as relevant to the developing analysis. Regular meetings of the qualitative team will take place throughout the data collection period to discuss the developing analysis and to make decisions about further data collection. Analysis will focus on understanding how the intervention was used and perceived at different points in time (pre‐surgery, whilst in hospital, shortly after coming home and after being at home for a while) and in different settings (the various hospital sites). To avoid losing important contextual details about the timepoint and setting in which each person's data were collected, a pen portrait analysis will be undertaken which draws out the narrative of how the intervention was used over time [14]. This involves identifying the core focus of the analysis (i.e., probably relating to acceptability and engagement with the intervention over time and across sites and how it was adapted). A template will be devised for capturing narrative summaries of the factors influencing acceptability, engagement and adaptations for staff and patients at each site. This will enable data from the interviews and observations to be pulled together to generate a rich understanding of the overall process in a way that facilitates understanding of similarities and differences between sites. Once a pen portrait has been generated for each site, an interpretation phase will occur in which the research team seek to explain why patients and staff engaged over time in the way that they did. These conceptual insights will be developed inductively, but may subsequently be mapped to Normalisation Process Theory [15] and the Theoretical Framework of Acceptability [16] to build our understanding. During the process of developing the pen portraits, we will hold a co‐analysis workshop in which provisional portraits will be reviewed and interpreted by a group of patient representatives.

Following an initial analysis of the qualitative and quantitative data, to obtain additional insights we will conduct a ‘following a thread’ mixed methods analysis. This involves generating questions raised by the results of one component and following ‘the thread’ across to the other component(s), for example looking for explanations in the qualitative data for patterns observed in the quantitative data.

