Previous studies exploring new information initiatives relevant to colorectal surgery are limited by a lack of evidence for their promise and plausibility. The clinical outcomes reported in these studies are also heterogeneous, often lacking considerations of patient‐centred benefit. The aim of this study is to explore the feasibility of the Recover Together intervention when deployed for the first time in the UK National Health Service (NHS). It also aims to explore the feasibility of key methods, including return rates for a series of patient‐centred outcome instruments and the return of data required to generate a robust evaluation of cost effectiveness in a future study.

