### Study design

This study is a mixed methods, feasibility study of a complex intervention developed for the purpose of improving recovery after oncological colorectal surgery. A total of 105 participants will be recruited from outpatient clinics across three to four study sites in the UK. After providing written informed consent, participants will receive each component of the Recover Together intervention at various timepoints, including around the time of their preoperative counselling and during their inpatient hospital admission. Participants will be followed up at 30 day and 6 month timepoints (Figure 1).

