Some issues of feasibility are beyond the scope of this work. First, the study is not designed to explore the feasibility of recruitment and retention, although participant screening data will provide some information about this. Instead, it is likely that recruitment and retention (including strategies to overcome hurdles) will be explored within an internal pilot phase of a potential definitive study. Secondly, the study is not designed to explore the feasibility of randomisation in a future study. Key considerations for a future trial will be the unit of randomisation (i.e., participants or clusters) along with statistical estimates of sample size and/or the intra‐cluster correlation coefficient. Finally, although the study will explore return rates of a series of patient‐centred outcome instruments, this will not determine the choice of a primary outcome. Instead, this will be determined between public representatives and the study management group in consultation with other key stakeholders to ensure that the final results are relevant and important to patients and the health service.

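### Without a control group, the planned comparison with published literature cannot show signals of patient benefit and should be presented as context only

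*Protocol article*

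**What the plan says.** The protocol article describes a single-arm study. Under Study design it states "A total of 105 participants will be recruited from outpatient clinics across three to four study sites in the UK", and that after consent "participants will receive each component of the Recover Together intervention at various timepoints". No comparison group is described, and the Discussion says that "the study is not designed to explore the feasibility of randomisation in a future study".

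Under Statistical and qualitative analysis, quantitative data are to be summarised as rates and means. Two sentences then follow one another: "No formal statistical comparisons or hypothesis testing will be conducted", and "Data will be compared with existing published literature to explore possible signals of patient benefit".

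Three other places bear on this:

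- **Aims and objectives** lists set-up time, fidelity, acceptability, engagement, training materials, completion of outcome instruments and missing cost data. Benefit to patients is not listed.
- **Progression criteria (Table 3)** uses set-up time, compliance with core processes, instrument return and cost or resource-use data. No row concerns outcome scores.
- **Abstract and Discussion** leave clinical and cost effectiveness to a later definitive study.

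**The concern.** The analysis paragraph rules out formal comparison and then gives an informal comparison a benefit purpose. A descriptive single-arm study can report scores, their spread and their completeness. It cannot say what the same patients would have scored without the intervention, and a published series does not supply that missing value.

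What is at stake is how the results are read. The Introduction criticises earlier information initiatives for lacking evidence of promise and plausibility, and the article's summary of what it adds presents this study as evaluating feasibility and plausibility. A favourable gap against published scores could easily be taken as that evidence. The planned mixed-methods step, which looks in the qualitative data for explanations of quantitative patterns, could then attach a convincing story to a difference that has nothing to do with the intervention. An unfavourable gap could equally be read as lack of promise.

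**Working it through.** **Can the design serve the stated purpose?** Write the observed gap as

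gap = intervention effect + population and care differences + measurement differences + sampling error.

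With one arm and an external mean, only the total is observed. The article itself shows where the middle terms could come from:

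- *Case mix.* Eligibility covers adults having elective surgery for confirmed or suspected colorectal cancer, with or without a stoma, and adds no further exclusions.
- *Site and background care.* Three to four hospitals that differ in organisation and volume take part. The Introduction describes enhanced recovery as standard care in many healthcare systems.
- *Measurement.* Table 2 has research staff administering instruments on the ward or in clinic, and follow-up by post, telephone or clinic.
- *Several readings.* Table 2 gives six post-surgery readings: satisfaction at day 1, QoR-15 at day 3, EQ-5D-5L at 30 days and 6 months, and WHO Disability Assessment Schedule and resource use at 6 months. The Discussion says the choice of primary outcome is left for later, so a signal could be looked for in any of them.

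Naming the comparator series in another document would not remove the middle terms.

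**How large would a difference have to be to mislead?** The article states no SD, effect size, error rate or derivation of 105, so there is no figure of its own to reproduce. What follows is an illustration.

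Inputs: n = 105 (Study design); n = 79, about 75% return (0.75 × 105 = 78.75, using the 75% boundary in Table 3); true intervention effect 0; published mean treated as fixed; favourable population difference b in SD units, **assumed**.

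Half-width of the 95% interval for a mean = 1.96/√n:

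- n = 105: 1.96/10.247 = 0.19 SD
- n = 79: 1.96/8.888 = 0.22 SD

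Probability that the whole interval lies on the favourable side = 1 − Φ(1.96 − b√n). Probability that the mean alone is favourable = Φ(b√n). For example, with b = 0.2 and n = 105, b√n = 2.049 and 1 − Φ(−0.089) = 0.54.

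| Assumed b (SD) | Whole interval favourable, n = 105 | Whole interval favourable, n = 79 | Mean favourable, n = 105 | Mean favourable, n = 79 |
|---|---|---|---|---|
| 0 | 0.025 | 0.025 | 0.50 | 0.50 |
| 0.1 | 0.17 | 0.14 | 0.85 | 0.81 |
| 0.2 | 0.54 | 0.43 | 0.98 | 0.96 |
| 0.3 | 0.87 | 0.76 | >0.99 | >0.99 |
| 0.5 | >0.99 | 0.99 | >0.99 | >0.99 |

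The calculation is symmetric. An unfavourable difference of the same size would give the same probabilities in the other direction, and could cancel a real effect. The table shows that a modest population difference could look like a signal. It does not show that such a difference exists.

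**The case against.** The strongest reply is that the sentence is already modest. It speaks of exploring possible signals, directly after formal comparison and testing have been ruled out. The instruments follow a recommended core outcome set, so published values for the same instruments may exist. Baselines are taken for QoR-15, EQ-5D-5L, the WHO Disability Assessment Schedule and resource use, and demographic and treatment data are collected, so comparability can be described. The choice of series may be set out in the full protocol or analysis plan, so its absence from the article is no fault.

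All of this stands, and it keeps the point small. It does not rescue the stated purpose. Hedged wording still names patient benefit as what the comparison is for, and a description of comparability does not identify an effect.

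Four stronger readings are tempting, and the article does not support them:

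- *That the article itself calls the comparison literature heterogeneous.* The sentence "The clinical outcomes reported in these studies are also heterogeneous" concerns earlier studies of information initiatives. The analysis section does not restrict the comparison to those studies.
- *That any signal would be case mix and not the intervention.* The effect cannot be identified. That does not make it absent.
- *That the comparator will be picked after the data are seen.* The article does not say when it will be chosen.
- *That an apparent benefit would drive progression.* The progression decision rests on the feasibility outcomes in Table 3, none of which is a benefit criterion.

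**Conclusion.** The point holds as a limited correction of wording. The article assigns the literature comparison a purpose that a single-arm design cannot serve and that its own objectives do not include. Any difference from published values could not be distinguished from differences in case mix, site, background care or questionnaire administration.

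The consequence is confined to what the study may conclude about benefit. Recruitment, data collection, the feasibility results and the decision to progress are unaffected. The illustrated probabilities rest on assumed population differences, a fixed published mean and a normal approximation. The conclusion does not depend on them, because it follows from the absence of a concurrent control.

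**What to change.** Replace the literature-comparison sentence under Statistical and qualitative analysis with:

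> Clinical outcome scores will be summarised descriptively (mean, SD, completeness, and change from baseline where a baseline exists) to inform a future trial. Any published values will be shown as context only, from series using the same instrument and timepoint in a similar surgical population, chosen before outcome data are summarised, and will not be interpreted as evidence of benefit.

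The cost is one sentence, with no change to recruitment, instruments or follow-up. The sponsor gives up an informal benefit reading, which is a small loss because effectiveness is already left to the definitive study.

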### Intervention refinement

Co‐design stakeholder workshops will be organised with surgeons, nurses and patients (two workshops with *n* = 9 participants) to refine the intervention (if required) and to refine training/implementation materials and processes. The first workshop will focus on identifying essential refinements based on qualitative and quantitative feasibility findings, and the second workshop will focus on ratification of the materials in preparation for the next stage of evaluation. The ratified training/implementation materials will feed directly into the future evaluation as an essential resource during site set‐up.

### Public and community involvement

A patient and public advisory panel has been convened to work closely with the study team throughout the study, including advising on data collection and recruitment processes, contributing to plain language versions of the study findings, developing recruitment materials, developing topic guides, interpreting data, and dissemination and engagement activities. In particular, the advisory panel will participate in a co‐analysis session to assist in the interpretation of the qualitative data and to inform the mixed methods analysis. A community group of members of the public who speak Urdu has also been convened. They will work with the study team to ensure that Urdu adapted materials are developed appropriately and further adapted based on feedback from the feasibility results.

## DISCUSSION

This study will explore the feasibility of implementing and evaluating the Recover Together intervention in NHS surgical practice. A series of quantitative and qualitative methods will explore the fidelity of each intervention component (booklet, video, goal board), reasons for adaptations and the impact of these, as well as acceptability of the components amongst patients and health professionals. The study will also explore the feasibility of administering a series of patient‐centred outcome instruments along with strategies to mitigate burden. Overall, this will refine the development of a future definitive study to explore the clinical and cost effectiveness of the Recover Together intervention, if shown to be feasible.

Patient counselling is a fundamental aspect of fast‐track recovery but little evidence exists to inform how it should be done in practice [4]. This is important so that pat**i**ents are enabled to participate actively in their recovery and to re‐engage with their everyday lives [17]. The Recover Together intervention was co‐produced by patients, health professionals and communication design experts to address common challenges identified in our previous engagement work. These included considerations around emotional stress precluding good understanding; poor information design; a lack of personalised content; missed opportunities to empower patients during their recovery; and poor availability of information after discharge [4]. Possible benefits for patients of addressing these challenges were shown to be an enhanced situated understanding of their care (i.e., familiarisation with the environment, events and people around them) and greater confidence to work with health professionals towards recovery goals [18]. Possible benefits for the NHS are reduced costs, reduced bed days, and greater capacity to provide cancer services in the setting of rapidly increasing demand.

Some issues of feasibility are beyond the scope of this work. First, the study is not designed to explore the feasibility of recruitment and retention, although participant screening data will provide some information about this. Instead, it is likely that recruitment and retention (including strategies to overcome hurdles) will be explored within an internal pilot phase of a potential definitive study. Secondly, the study is not designed to explore the feasibility of randomisation in a future study. Key considerations for a future trial will be the unit of randomisation (i.e., participants or clusters) along with statistical estimates of sample size and/or the intra‐cluster correlation coefficient. Finally, although the study will explore return rates of a series of patient‐centred outcome instruments, this will not determine the choice of a primary outcome. Instead, this will be determined between public representatives and the study management group in consultation with other key stakeholders to ensure that the final results are relevant and important to patients and the health service.

## STUDY SPONSOR

University of Leeds.

## PROTOCOL VERSION

v1.1.

## DATA MONITORING

As a feasibility study of a low‐risk intervention, a data monitoring committee has not been recruited for the purpose of this study.

## DISSEMINATION

The final results will be disseminated via academic conferences, learned publications and social media channels.

## Data Availability

Data sharing is not applicable to this article as no new data were created or analyzed in this study.
